### Blinding and Risk of Contamination

Patients, relatives, and health care professional participants are not explicitly informed about ward allocation in the study information materials. It was not specified whether the respondents were on an intervention or control ward. Health care professionals are not actively informed about the group assignment either. However, as a psychologist is permanently integrated into the team on intervention wards, group assignment can still be inferred based on the care structure. The project management, ward management, and the study therapist were informed about the group assignment; further communication of the assignment was avoided. Full blinding of health care professionals to group allocation is not feasible in this trial because the permanent integration of a study therapist on intervention wards is visible in daily practice. By contrast, patients and relatives are not explicitly informed about the intervention content or their group assignment. In the informed consent materials, all participating wards are described as providing psychosocial care, and the study is presented as an investigation of emotional health during and after intensive care. Because most patients receive treatment on only one ICU ward and transfers between participating ICUs are rare, they have no direct comparison standard and are therefore unlikely to distinguish intervention from usual care conditions.

To minimize contamination at the organizational level, study therapists are exclusively assigned to intervention wards and do not provide structured psychosocial counseling on control wards. Existing consultation-liaison services on control wards continue unchanged, without additional involvement from the IPS-Pilot team. Any observations deviating from our expectations will be documented via the process documentation.

### Intervention

In the intervention units, study therapists are permanently integrated into the treatment teams with a half-time position. They provide psychosocial support to patients, relatives, and health care professionals and offer various intervention components adapted to individual needs. These components, along with the role and stance of the study therapists, are specified in the IPS intervention manual.

Before the study onset, the study therapists underwent standardized training that included medical fundamentals, typical stressors in ICUs, and the practical application of the intervention manual. Quality assurance is supported through regular external supervision and peer intervision, which alternated weekly.

### Comparison Condition

In the control group, psychosocial care continues to be provided by existing psychosocial services (eg, the consultation service), but without the permanent integration of a psychologist into the team.

### Pilot Effectiveness Evaluation

#### Overview

Although the intervention and its evaluation are closely linked, they represent 2 methodologically distinct components of the project. The intervention involves the permanent integration of clinical study therapists into the intensive care team.

The accompanying study systematically evaluates the feasibility of conducting an RCT to evaluate the intervention. Key criteria for the feasibility of the RCT include participation and dropout rates, data completeness, and the overall practicability of the administered questionnaire. The feasibility of the intervention is assessed in terms of participation, dropout rates, fidelity, and acceptance. Both quantitative and qualitative methods are applied.

The study is aimed at 3 groups in intensive care: patients, their relatives, and health care professionals.

Planned sample sizes are (1) up to 125 patients and their relatives during the course of the study, and (2) approximately 250 health care professionals. The planned sample size is based on feasibility considerations rather than a formal statistical power calculation. In line with recommendations for pilot and feasibility trials, the sample is intended to provide sufficient information on recruitment processes, data completeness, and variability of candidate outcome measures to inform the design of a subsequent definitive trial.

The standardized survey is conducted with health care professionals at 2 measurement points: a baseline survey (*t*_0_), which is administered within 6 weeks of the start of the intervention for health care professionals and a second survey (*t*_1_) at the end of the intervention phase. Relatives and patients are recruited during the patient’s ICU stay; however, only for relatives, a baseline survey (*t*_0_) is administered during that time to avoid placing a high burden on patients. The follow-up survey (*t*_1_) is conducted with relatives and patients 4 months after discharge from the ICU.

#### Inclusion and Exclusion Criteria

General ICUs for adults that had a defined minimum number of treatment places and whose hospital management had expressly agreed to participate in the study were included. Only adult individuals (≥18 y) with the capacity to provide informed consent were eligible to participate in the survey. However, specialized ICUs that already had firmly established integrated psychosocial care structures and wards where other psychosocial intervention studies were being conducted in parallel were excluded.

Participation in the survey is voluntary and takes place regardless of whether the intervention has been used individually. The aim is to systematically assess the potential effects of the intervention from the perspective of all groups involved, using scales that could be used in a future RCT.

#### Measures

The data collected will be used to assess which dimensions could be suitable as primary or secondary end points for a subsequent effectiveness study—for example, subjective well-being, perceived stress, or aspects of the team climate.

At present, no core outcome set exists for psychosocial health in intensive care settings, and there is no consensus on how changes in psychosocial burden among patients, relatives, or health care professionals should be assessed. For this reason, a broad set of theoretically grounded candidate outcomes is required to capture the multidimensional nature of psychosocial strain and recovery in this context.

The selection of multiple psychosocial outcomes reflects the complex and multilevel nature of psychosocial burden in the ICU context, which affects individual well-being, symptoms of anxiety and depression, perceived stress, and team processes among health care professionals. Combining generic well-being and health-related quality of life measures (World Health Organization–Five Well-Being Index [WHO-5] and 12-Item Short Form Health Survey [SF-12]) with brief symptom scales (Patient Health Questionnaire–4 [PHQ-4] and Perceived Stress Scale–10 [PSS-10]) and work-related constructs (psychosocial safety climate, team cohesion, and irritation) allows us to capture different, theoretically grounded dimensions that may respond differentially to the intervention [12,13,20-28]. In line with recommendations for feasibility studies of complex interventions [14,18], this broad set of candidate outcomes will be used to evaluate acceptability, completeness, and distributional properties, and to inform the selection of a smaller number of primary and key secondary endpoints for a future definitive trial. The aim was an economical but, at the same time, differentiated survey of psychosocial stress and well-being dimensions, which could also be considered relevant target variables for a later main study. Given the feasibility focus of this pilot trial, all analyses will be primarily descriptive. Feasibility outcomes (eg, participation rates, drop-out rates, and data completeness) will be summarized using absolute and relative frequencies, as well as means with SDs or medians with IQRs, as appropriate. No formal hypothesis testing or confirmatory effectiveness analyses are planned. Exploratory analyses of candidate outcome measures will be conducted to assess distributional properties and missingness, with the aim of informing endpoint selection for a subsequent definitive trial.

The following questionnaires are used for health care professionals: WHO-5 [20], Psychosocial Safety Climate Questionnaire [21], Questionnaire for Self-Efficacy, Optimism, and Pessimism [22], SF-12 [23], PSS-10 [24], PHQ-4 [25], Erlangen Team Cohesion at Work Scale (validated German version) [16], Irritation Scale for work-related stress consequences [27], and Intention to Leave (items from the NEXT-study) [29]. For patients and relatives, the following questionnaires are used: WHO-5 [20], SF-12 [23], PSS-10 [24], and PHQ-4 [25].

Sociodemographic data such as age, gender, education, professional experience (health care professionals), stay in the ICU (patients and relatives), psychological stress in ICUs, and use of psychosocial support services are collected. In addition to the standardized survey instruments (eg, WHO-5, SF-12, PHQ-4, and PSS-10) and sociodemographic questions, additional questions developed specifically for the target group are collected. These include evaluative assessments of the comprehensibility, relevance, and reasonableness of the individual parts of the questionnaire, as well as attitudes toward psychosocial care in ICUs (eg, the involvement of a ward psychologist or the use of support services).

The additional questions are worded specifically for the target group (health care professionals vs relatives) and embedded within the respective questionnaire structure. A standardized scale was used particularly for the evaluation questions (Likert scales); open text fields are also provided. These items were developed within the project and do not appear as an independent questionnaire, but rather supplement the standardized instruments in a context-sensitive manner.

### Feasibility Evaluation

A key aim of this pilot study is to assess whether psychosocial outcomes can be reliably and meaningfully recorded under RCT conditions, alongside the technical feasibility of data collection, recruitment and dropout rates, and data completeness, and whether the IPS intervention is feasible in terms of participation, dropout, intervention fidelity, and acceptance. In line with methodological guidance on pilot studies and progression criteria for complex interventions [14,18], the predefined thresholds are therefore not treated as rigid statistical decision rules but as pragmatic benchmarks to judge whether a full-scale RCT appears feasible and justifiable.

For the subsequent definitive trial, we will apply a structured “traffic light” progression framework:

Proceed: if participation rates in all stakeholder groups are 80% or more, dropout is 35% or less, and missing data on core outcome variables are 20% or less, we will consider the trial design and intervention feasible without major modifications.Proceed with modifications: if participation rates are between 60% and 79% and/or missing data are between 21% and 30%, we will identify and address modifiable barriers (eg, recruitment processes and questionnaire length) before progressing to a full RCT.Do not proceed as planned: if participation rates fall below 60% in key groups or if missing data on core outcomes exceed 30%, a definitive RCT in its current form will not be recommended; instead, additional developmental work or alternative evaluation designs will be considered.

This framework allows us to combine quantitative feasibility indicators with qualitative insights from the process evaluation, enabling us to reach a transparent and evidence-informed decision on whether and how to progress to a subsequent effectiveness trial.

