#### Dropout Rate

We define dropout as incomplete participation between *t*_0_ and *t*_1_ among those who had originally agreed to participate. For health care professionals and relatives, dropout is assessed across the 2 survey time points; for patients, it refers to the ratio of respondents in the survey (*t*_1_) to the number of recruited patients who provided informed consent during their ICU stay. The dropout rate should not exceed 35% of those who originally consented [30,34,36].

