#### Data Completeness

Another important criterion is the completeness of data collection. For each target group and survey time point, the proportion of missing data will be monitored and reported. Acceptable thresholds are 20% or less missing data for core outcome variables [38].

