#### Fidelity

Fidelity refers to the extent to which the intervention was implemented as intended. This includes adherence to the intervention manual, the documented presence of study therapists according to duty rosters, the correct implementation of intervention modules (eg, delirium prevention and grief counseling), and weekly self-assessments by study therapists regarding their team integration. All procedures are documented centrally and monitored for deviations. A fidelity rate of 80% or more across these components is targeted [31,36,37].

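### The traffic-light progression rule is incomplete and overlapping: dropout above 35% has no amber or red consequence, amber and red can both apply, the key groups are unnamed, and green declares the intervention feasible without its own targets

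*Protocol article*

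**What the plan says.** The rule is in the protocol article under Feasibility Evaluation.

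- **Green** applies "if participation rates in all stakeholder groups are 80% or more, dropout is 35% or less, and missing data on core outcome variables are 20" percent or less. The conclusion is then: "we will consider the trial design and intervention feasible without major modifications".
- **Amber** is "Proceed with modifications: if participation rates are between 60% and 79% and/or missing data are between 21% and 30" percent.
- **Red** applies "if participation rates fall below 60% in key groups or if missing data on core outcomes exceed 30" percent.

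The section introduces the thresholds as "not treated as rigid statistical decision rules but as pragmatic benchmarks". It also describes the framework as structured, and expects it to lead to a transparent decision that draws on the qualitative findings as well.

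Other sections supply the definitions and targets:

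- Dropout Rate (under Feasibility of an RCT): "The dropout rate should not exceed 35% of those who originally consented".
- Data Completeness: "For each target group and survey time point, the proportion of missing data will be monitored and reported", with a limit of 20% for core outcomes.
- Definition of Participation Rate: for professionals and relatives, participation means the baseline survey, and completion of t1 is handled in the dropout analysis. For patients, participation means completing t1, their only survey.
- Fidelity: "A fidelity rate of 80% or more across these components is targeted". Acceptance: at least 70% favourable helpfulness ratings.

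**The concern.** Whether a pragmatic RCT is feasible is the primary research question, and this rule is the stated route to the answer. A progression rule should give each result one colour, and each criterion with a limit should have a consequence when that limit is broken. This rule does neither for dropout, which is one of the four core criteria for feasibility of the RCT. It also leaves open which of two colours prevails, and which groups can turn the verdict red. Those choices would then be made with the results in view.

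The green verdict covers two things, the trial design and the intervention, but its conditions concern only survey participation, survey dropout and survey missingness. The same section says the intervention is to be judged on fidelity and acceptance as well.

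**Working it through.** There is no sample size or power figure to reproduce. The check is to apply the three rows literally.

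**Step 1. The rows side by side.**

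| Criterion | Green | Amber | Red |
|---|---|---|---|
| Participation | 80% or more, all groups | 60–79%, groups not specified | below 60%, key groups |
| Dropout | 35% or less | none | none |
| Missing core outcomes | 20% or less | 21–30% | above 30% |
| Fidelity (target 80% or more) | none | none | none |
| Acceptance (target 70% or more) | none | none | none |

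**Step 2. Results without a colour.** Take participation 85%, missing data 10%, dropout 40%. Green fails on dropout, and the conditions for amber and red are not met. The same holds at 90% dropout. For one group, with each rate a whole percentage from 0 to 100, the uncoloured cells are those with participation 80–100 (21 values), dropout 36–100 (65 values) and missing data 0–20 (21 values): 21 × 65 × 21 = 28,665 of 101³ = 1,030,301. Outside that region participation and missing data set the colour, and dropout above 35% changes nothing.

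**Step 3. Which groups this affects.** For professionals and relatives, participation is fixed at t0, so loss by t1 can show only as dropout. For patients, t1 non-response lowers participation itself. An uncoloured patient result needs at least 0.80 × 125 = 100 respondents together with dropout above 35%, which means more than 100/0.65 = 153.8 consents against a planned maximum of 125. The gap hardly binds for patients.

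**Step 4. Results with two colours.** Participation 70% with missing data 35% meets amber on the first and red on the second. Participation 50% with missing data 25% does the reverse. On the same grid:

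- participation 60–79 with missing data 31–100: 20 × 70 × 101 = 141,400
- participation 0–59 with missing data 21–30: 60 × 10 × 101 = 60,600
- total 202,000 cells that are both amber and red.

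These counts describe the logic of the rule. They are not probabilities.

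**Step 5. Gaps between bands.** 199/250 = 79.6% participation is below green and above amber. Missing data of 20.5% is above green and below amber.

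**Step 6. The article's own counts.** Target Participation Rates relates the rates to the planned numbers, taken here as 250 professionals, 125 relatives and 125 patients. The counts come from the Results section.

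- Professionals at t0: 177/250 = 70.8%, amber.
- Relatives at t0 (fully completed questionnaires): 82/125 = 65.6%, amber.
- Patients: 72 consents by May 2025. If all respond and no more consent, 72/125 = 57.6%. The 60% line is 0.60 × 125 = 75 respondents, so this is three short.

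If patients are a key group, the participation results are amber and red at once. If they are not, the participation results are amber.

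**Step 7. The intervention verdict.** As the table shows, no colour depends on fidelity or acceptance. Green can be reached at any value of either, including 0%.

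**The case against.** The strongest reply is that the section disclaims a mechanical algorithm: the thresholds are benchmarks, analyses are descriptive, and qualitative findings also count. This stands in part. It would be too strong to infer that no sound progression decision can be reached. But latitude to depart from a colour does not supply a colour where none is given, choose between two, or name the key groups, and the section itself promises structure and transparency.

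A second reply is that worst colour wins is the natural reading, since a result meeting the red condition would not be recommended. That would settle the overlap, but it is not written, and it cures neither the dropout gap nor the intervention verdict.

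A third is that fidelity and acceptance are assessed in their own sections. They are, so the defect lies in the reach of the green sentence and not in a missing assessment.

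Four stronger readings are tempting and are not supported:

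- **Dropout as the criterion most likely to fail.** The article cites comparable trials with dropout of around 20% to 30%, inside the limit. Its few t1 returns so far are interim and cannot be read as dropout.
- **Only 0.80 × 0.65 × 0.80 = 41.6% of the planned number usable at the green limits.** For patients this counts t1 non-response twice; without the dropout factor the product is 0.80 × 0.80 = 64%. It also treats 20% missing data as 20% of respondents being unusable, which the article does not say.
- **Dropout of 31–35% is acceptable as dropout yet red as missing data.** This requires unreturned t1 questionnaires to count as missing. The article lists dropout and completeness as separate criteria and puts t1 completion in the dropout analysis, which points the other way. A one-sentence definition would close the question.
- **A false green is imminent.** With professionals' and relatives' baseline recruitment reported complete at 70.8% and 65.6%, green already looks out of reach. The live question is amber against red.

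**Conclusion.** The point holds in this form and should be fixed; it does not invalidate the trial. For professionals and relatives, dropout above 35% can block green but cannot prompt modification or stopping, and it leaves the result uncoloured when the other two criteria are in the green range. Amber and red overlap without a stated order, the bands are not contiguous, and the green sentence certifies the intervention on criteria that do not measure its delivery or acceptance.

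The practical weight lies in the undefined key groups: at 70.8%, 65.6% and at most 57.6%, the status of patients could decide amber or red. This assumes denominators of 250, 125 and 125, that amber is triggered by any group in its range, that the 82 fully completed relatives' questionnaires represent participation, and that patient consents stay at the interim 72.

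**What to change.** Amend the progression wording before analysis, and date the amendment as made after interim counts were public.

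1. State that the worst criterion sets the overall colour.
2. Make the bands contiguous: amber is 60% to below 80% participation, and above 20% to 30% missing data.
3. Make dropout above 35% at least amber. Any red cut for dropout is for the sponsor to set and justify; the article offers no figure for one.
4. Name the key groups, or apply red to all three groups.
5. Define missing data as missing core outcomes among returned questionnaires, and report beside it the share of consenters with usable t1 data.
6. Either remove the intervention from the green sentence, or also require the fidelity and acceptance targets there.

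The cost is wording only, with no new data. The downside is that green becomes harder to reach. A red verdict may also follow from counts already known if red is applied to patients, which is why the date of the change and the reason for it should be on record.

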### Qualitative Evaluation of Study Participation

As part of the qualitative accompanying research, additional data are collected on how patients, relatives, and health care professionals perceive the approach to participate in the study, especially in the context of the particularly stressful situation in an ICU. These assessments are derived from the qualitative process evaluation and informal feedback, complementing the evaluation of the practicability and ethical acceptance of the survey instruments, and do not constitute a separate qualitative study component.

### Feasibility of an RCT

#### Overview

The feasibility of the planned study procedures under real clinical conditions is assessed. The assessment of feasibility focuses on 4 core criteria: participation rate, dropout rate, practicability of the survey, and data completeness, as defined in the study registration. The predefined thresholds for participation rates, dropout rates, and data completeness were informed by previous feasibility and pilot trials of psychosocial and organizational interventions in intensive care and acute care settings, which typically report participation rates between 70% and 90% and dropout rates around 20% to 30% across follow-up assessments [30-37].

